## Abstract

New biologic and small molecule targeted agents have expanded the armamentarium of Spondyloarthritides (SpA), allowing more therapeutic options for patients who do not respond to therapy. The implementation of the treat-to-target (T2T) strategy with close monitoring and frequent treatment adaptations targeting disease remission has been proposed as the means to prevent radiographic progression and long-term adverse outcomes. In this project we will employ the “University of Crete Rheumatology Clinic Registry” to prospectively study in real-world practice musculoskeletal and extraarticular disease activity, patient function, comorbidities, sociodemographics, imaging, compliance to therapy and other lifestyle factors in axial and peripheral SpA patients. The predictive value of these variables in long-term (2years) outcomes will be evaluated. We will also assess the implementation of the T2T approach as well as its impact on long-term patients’ outcomes (quality of life, productivity, adverse events). The successful completion of this study could pave the way for improved and personalized therapy in patients with SpA.

## BACKGROUND AND STUDY RATIONALE

Spondyloarthritides (SpA) are chronic diseases which cause inflammation at musculoskeletal as well as extraarticular sites, resulting in heterogeneous clinical phenotypes and variable organ damage. SpA are usually diagnosed in young to middle-aged adults and severely impact patients’ quality of life thereafter by the significant decline in physical function and their capacity to work. The chronic inflammatory state of SpA, as well as the cumulative drug exposure are also associated with a higher incidence of comorbidities in these patients, such as accelerated atherosclerosis with resultant cardiovascular disease, metabolic syndrome, osteoporosis with fractures and gastroduodenal ulcers.^1^ In addition, SpA are associated with a profound psychological burden, with high prevalence of depression and anxiety,^2^ as well as widespread musculoskeletal pain (fibromyalgia) caused by central pain sensitisation.^3^

Important steps to improve the management and outcomes of patients with SpA have been accomplished over the past decades, most notably by the development of validated, reliable metrics for the assessment of disease activity which directly relate to long-term outcomes and the recognition of the importance of early diagnosis and prompt initiation of effective therapy.^4^ Moreover, the concept of tight follow-up of patients with appropriate treatment adaptations in a treat-to-target (T2T) approach has also been introduced.^5,6^ In this regard, disease remission (or at least low disease activity) is the aim of therapy and the only means to prevent radiographic progression and long-term adverse outcomes.^7^

These steps were complemented by the breakthrough expansion of the therapeutic armamentarium for SpA, which now includes not only non-steroidal anti-inflammatory drugs (NSAIDs) and conventional synthetic disease modifying antirheumatic drugs (csDMARDs), but also biologic DMARDs (bDMARDs) and, recently, targeted synthetic DMARDs (tsDMARDs).^8,9^

Notwithstanding these important steps, many patients of everyday clinical practice do not achieve low disease activity (LDA), let alone remission, even with the newest bDMARD and tsDMARD therapies.^10^ In a recent analysis of SpA patients from the Hellenic Registry of Biologic Therapies (HeRBT) from 8 rheumatologic centres in Greece it was found that 58% of patients with axial disease and 80% of patients with peripheral joint involvement never achieve a state of inactive disease at any time point within the 1st year of TNFi therapy.^11^ In these patients it is not known if a T2T strategy was implemented as the T2T recommendations by the European Rheumatology Society (EULAR) were only recently issued.^12,13^ and the feasibility, as well as the efficacy of the proposed strategy is still not well documented. In another analysis of the same registry for patients with rheumatoid arthritis (RA) on bDMARDs, not achieving sustained low disease activity or remission had adverse impact on long-term patient function and the accrual of serious adverse events.^14^ However, in SpA there are no studies comparing long-term outcomes (beyond one year of therapy) of patients treated to target compared to those of usual practice.

SpA patients are frequently treated with high-cost drugs, resulting in a significant financial burden on healthcare system.^15^ Using these drugs in patients who will not respond to therapy, besides the significant cost, places patients in potential risks without benefit. Multiple RCTs and registry studies have explored for potential predictors of response to treatment with bDMARDs. Male sex, higher C-reactive protein (CRP) and better function at treatment start were associated with better response to therapy in axial SpA (AxSpA), however with a moderate effect size.^11,16^ Strong –and preferably modifiable – clinical variables at baseline or during therapy that can determine the outcome are not yet known.

Comorbidities in patients with SpA have been shown to have an adverse impact on many patient outcomes, such as functional disability, quality of life, work productivity and mortality.^17–19^ Comorbidities can also affect adverse event incidence during treatment, such as infections. The predictive value of higher comorbidity index on treatment response in SpA patients has not been sufficiently studied, however, recent studies from registries indicate that comorbidities may affect short-term response to therapy with TNFi^20,21^ and more research in this direction is necessary.

Treatment response could also be affected by sociodemographic factors (eg, education, employment), patient lifestyle (exercise, diet, and smoking),^22–24^ and by compliance to therapy. Even though most data come from studies in RA patients, it is shown that there is a high rate of therapy non-compliance^25^ and this could have an adverse impact on long-term prognosis.^26^ EULAR has highlighted the importance of patient education regarding their disease course and management and the effective implementation of lifestyle changes that can improve outcomes, such as exercise and smoking cessation in its recent recommendations.^27–29^

In addition to randomised clinical trials (RCTs), well-structured patient registries are important tools to evaluate treatment effects in “real-world” patients and provide with answers to many types of research questions relevant to clinicians.^30^ Advantages of registries include the diverse population of patients assessed in daily practice, many of which would be excluded from RCTs due to their stringent exclusion criteria (eg, patients with co-morbidities, non-compliance, or specific previous or ongoing co-therapies),^31^ the long follow-up time of monitoring and the possibility to explore for new associations, or predictors of a treatment outcome.

## AIMS OF THE STUDY

The aims of the present study are:
To assess the extent of the implementation of T2T strategy in SpA patients of real-world practice, to explore the reasons of possible non-implementation and to evaluate the impact of this therapeutic strategy in the long-term (2 year) prognosis of these patients compared to usual practice.To use validated metrics and collect prospective, accurate, relevant, complete, and up-to-date data of disease parameters, comorbidities and patient lifestyle factors and compliance and evaluate their predictive effect on disease outcomes (safety, function, quality of life, productivity and health indices) in SpA patients starting/switching to a new therapy.

## METHODS

### Study design

This study has a prospective design, and it will take place in the Rheumatology Department of the University Hospital of Heraklion and the University of Crete, Medical School. It has been approved by the Ethics Committee of the University Hospital of Heraklion. Consecutive patients will be enrolled, after their consent, according to the following inclusion criteria: a) adult (≥18 years old) patients with AxSpA or peripheral SpA (perSpA) including psoriatic arthritis (PsA) diagnosed by a rheumatologist, b) regular follow-up at the outpatient department of our hospital or the Rheumatology one-day infusions’ Clinic, and at least 1 visit within the first semester of the study, and c) any prescribed therapy for SpA including NSAIDs, csDMARDs, bDMARDs, or tsDMARDs.

Questionnaires regarding patient characteristics, comorbidities, and disease and treatment characteristics will be collected from patients and physicians at baseline (specific parameters outlined below). After recruitment (months 0 - 6), patients will be prospectively followed-up for 2 years (months 7 – 30) and the implementation of T2T strategy or not (and reasons) will be monitored, along with patient reported outcomes and disease activity scores at specific timepoints (outlined below). Additionally, all adverse events and treatment switches will be recorded at the time they occurred.

A target of at least LDA, based on Ankylosing Spondylitis Disease Activity Score (ASDAS) in AxSpA patients and Disease Activity In Psoriatic Arthritis (DAPSA) index in peripheral SpA and PsA patients will be set for all patients. A follow-up will be considered as compatible with the T2T recommendations if: (a) the patient is re-evaluated within 3 or 6 months according to the guidelines (see below) and (b) disease activity measured using the aforementioned indices is used as a guidance for any necessary treatment modifications. The T2T approach requires adaptation of treatment using the best available therapeutic choices when a patient has not reached the predefined treatment target. In this study, treatment modifications will include increasing the dosage, addition or switching to a new b-/ts-/csDMARD(s), administration of NSAIDs (in AxSpA) and short-course systemic corticosteroids (in PerSpA) or intraarticular steroid injections (in both AxSpA and PerSpA).

### Follow-up intervals and variables collected

As this is a non-interventional study, patient re-assessment intervals will follow the nationally and internationally-issued guidelines, according to which patients with moderate or high disease activity should be re-assessed every (maximum) 3 months, while patients with low disease activity or remission may be re-evaluated every 6 months. From each patient, the following variables will be collected at inclusion visit and/or at regular (3-6-month) follow-up intervals:
**Patient characteristics**: Socio-demographics (gender, date of birth, education, employment, residence, marital status) and lifestyle (smoking, alcohol, exercise, diet).**Disease characteristics**: Date of diagnosis, axial and/or peripheral disease involvement, extraarticular manifestations, SpA classification criteria, imaging (X-Rays and MRI), disease activity and patient function indices (BASDAI, ASDAS,^32^ BASFI,^33^ HAQ,^34^ DAS28, DAPSA^35^) and extraarticular manifestations’ activity indices [psoriasis body surface area (BSA), LEI,^36^ dactylitis count, Inflammatory Bowel Disease flare and uveitis flare (Yes/No)].**Treatment characteristics**: Previous treatments (drugs, treatment duration, reason of stop), ongoing drugs (name and dosage of main and concomitant disease treatments, treatment discontinuations and reasons), and compliance to ongoing therapy (MARS-5).^37^**Quality of life, productivity and health Indices:** EuroQol 5D (EQ-5D), ASAS-HI,^38^ PSAID,^39^ Hospital Anxiety and Depression Scale (HADS) and Work Productivity and Activity Impairment questionnaire (WPAI).**Comorbidities:** All comorbidities, with an emphasis on those included in the Rheumatic Disease Comorbidity Index (RDCI).^40^**Adverse events**: All adverse events occurring during follow-up (MedDRA recording system; https://www. meddra.org/faq/meddra-general); grading according to Common Terminology Criteria for Adverse Events (CTCAE) v.5.

Finally, a questionnaire (provided in the **Supplemmentary File**) will be filled by treating physicians after each patient encounter regarding the application of the T2T approach and the reason this might not be applicable or feasible in those patients whose therapy is not intensified despite non achievement of therapy targets.

### Database

Data will be captured using the University of Crete Rheumatology Clinic Registry (UCRCR), a web-based platform developed in collaboration with the Center for eHealth Applications and Services (CeHA) at the Institute of Computer Science, Foundation for Research and Technology – Hellas (ICS-FORTH). UCRCR employs strict security specifications and anonymized patient data, in line with the General Data Protection Regulation (GDPR) and serves as a tool for monitoring patients with immune-mediated systemic diseases of single-center as well as multicenter studies. The database is built to manage a vast array of heterogeneous patient and disease related data and follow-up their changes in time, while it allows for real-time customised exports of data for further analysis.

### Study outcomes

We will assess for the attainment of low disease activity and remission, as well as other treatment outcomes (quality of life, health and function indices, productivity, and adverse events) in patients who were treated or not treated based on the T2T recommendations. As this is not an interventional trial, the length of time over the two years that a patient was followed according to the T2T strategy will be used to classify patients between the T2T and non-T2T strategy. We also plan to evaluate the burden of comorbidities in these patients and its accrual during the study and patient compliance to therapy. Predictors of treatment response will be sought among these and other baseline and early on-treatment variables.

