### Statistical analysis

Statistical analysis (months 31–36) will include descriptive results on demographics, proportion of patients with low disease activity and remission, comorbidity indices, compliance, and the implementation of the T2T strategy. Multivariable regression and mixed effects models will be employed to explore predictors of attainment of treatment targets and of long-term (2-year) treatment outcomes among baseline and early on-treatment clinical and demographic characteristics. Due to the phenotypic heterogeneity of SpA, we aim to enroll at least 300 patients, which will allow for statistically robust results to be obtained.

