## ANTICIPATED RESULTS AND PROJECT SIGNIFICANCE

Complementary to randomised controlled trials, registry-based studies of real-world patients are important tools to assess long-term effectiveness, safety and pharmacoeconomic data when new therapies and treatment strategies are applied, while they can correlate clinical response with parameters such as comorbidities, co-administered therapies and patient’s compliance. The treat-to-target approach has been found effective in RA and there are indications that it can be effective also in SpA patients, although this is not yet proven.

The significance of the study lies in the following aspects:
We will quantify the level of effective control of inflammatory burden in patients with SpA in daily practice.The level of the T2T strategy implementation and the reasons for non-implementation in patients who have not reached treatment targets will be evaluated.The study will assess factors which could possibly be associated with treatment response in SpA, such as several validated disease indices, treatment characteristics and non-commonly collected clinical and patient variables, like comorbidities, sociodemographics and compliance.The predictive value of these factors and the evaluation of the effectiveness of the T2T approach regarding long-term patient outcomes will be explored.

Thus, the successful completion of this study could pave the way for improved and personalised therapy in patients with SpA.

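### Classifying patients as T2T or non-T2T by length of T2T follow-up discards a graded exposure and, if benefit rises with the amount of T2T, loses precision for the first aim

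*Protocol article*

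**What the plan says.** All references are to the protocol article.

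- **Unit of scoring (Study design).** "A follow-up will be considered as compatible with the T2T recommendations if" two conditions hold: re-evaluation within the guideline interval of 3 or 6 months, and use of the disease activity index to guide any treatment change. This is a rule for a single follow-up.
- **Duration and spacing.** In Study design, "patients will be prospectively followed-up for 2 years". Follow-up intervals and variables collected sets "regular (3-6-month) follow-up intervals".
- **Patient-level exposure (Study outcomes).** "the length of time over the two years that a patient was followed according to the T2T strategy will be used to classify patients". The purpose is to "classify patients between the T2T and non-T2T strategy", and several outcomes are to be assessed "in patients who were treated or not treated based on the T2T recommendations".
- **Models and size (Statistical analysis).** Multivariable regression and mixed effects models are planned for baseline and early on-treatment predictors. T2T time is not named as a continuous exposure, nor is it excluded. On size, "we aim to enroll at least 300 patients, which will allow for statistically robust results to be obtained".
- **Role of the contrast.** The impact of T2T on two-year prognosis, against usual practice, is part of the first aim. Under Anticipated results and project significance, "the evaluation of the effectiveness of the T2T approach regarding long-term patient outcomes will be explored".

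**The concern.** The plan measures a quantity, the amount of follow-up that met the T2T rule, and then commits to analysing it as a label with two values. Patients just either side of the cut fall into opposite groups, while patients with widely different amounts of T2T on the same side count as identical. A threshold written in a fuller document would settle where the cut lies but would not remove this.

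What is at stake is precision on the first aim. If the effect of T2T grows with the amount received, part of the variation that could reveal it is discarded, and the 300 patients carry the information of a smaller study.

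**Working it through.** **Inputs from the protocol article**
- Follow-up: 24 months. Visit spacing: 3 to 6 months. Scored intervals per patient: 24/6 = 4 to 24/3 = 8.
- Enrolment: at least 300.
- Not stated: significance level, power, effect size, distribution of T2T time, shape of the exposure-outcome relation. The figure of 300 therefore cannot be reproduced, and everything below is conditional on stated assumptions.

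**Measure of loss.** Let X be a patient's share of T2T-compatible time, c the cut, and D = 1 if X is at or above c. Under a linear effect of X, the fraction of exposure information kept by analysing D instead of X is corr(X, D)².

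**Step 1: continuous share, uniform on 0 to 1.**
Cov(X, D) = c(1−c)/2, Var(X) = 1/12 and Var(D) = c(1−c), so

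corr² = [c²(1−c)²/4] / [c(1−c)/12] = 3c(1−c).

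| Cut | Kept | Lost | 300 act like |
|---|---|---|---|
| 50% | 3 × 0.50 × 0.50 = 0.75 | 25% | 225 |
| 75% | 3 × 0.75 × 0.25 = 0.5625 | 44% | 169 |
| 80% | 3 × 0.80 × 0.20 = 0.48 | 52% | 144 |

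**Step 2: the share as visits would produce it.** Take 0 to 8 compatible quarters, equally likely. Then Var(X) = (81−1)/12 = 6.667 in quarters². With p the proportion at or above the cut and d the difference in mean X between the groups, corr² = p(1−p)d²/Var(X).
- Cut at 50% (4 or more): p = 5/9, d = 6 − 1.5 = 4.5. Kept = (20/81) × 20.25/6.667 = 0.75; lost 25%.
- Cut at 75% (6 or more): p = 3/9, d = 7 − 2.5 = 4.5. Kept = (18/81) × 20.25/6.667 = 0.675; lost 32.5%; 300 × 0.675 ≈ 203.
- Cut at 100%: p = 1/9, d = 8 − 3.5 = 4.5. Kept = (8/81) × 20.25/6.667 = 0.30; lost 70%.

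On a scale of 0 to 4 half-years, the same calculation gives 25% lost at 50% and at 75%, and 50% lost at 100%.

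**Step 3: other assumed distributions (simulated draws, linear effect).**
- Shares skewed towards high adherence, Beta(2,1) and Beta(3,1.5): 33–39% lost at a 50% cut, 36–39% at a 75% cut.
- Normal: 36% lost at a median cut, 51% at the 20th or 80th percentile.
- All shapes tried (uniform, normal, skewed, U-shaped), cuts from the 20th to the 90th percentile: about 19% (U-shaped, median) to 79% (U-shaped, 90th percentile).
- True effect a step exactly at the cut: no loss.

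**Step 4: meaning for power.** Suppose the continuous analysis had 80% power at two-sided 0.05 (both assumed). Power after dichotomising is Φ(2.802 × √kept − 1.960):
- kept 0.75: Φ(2.426 − 1.960) = 68%
- kept 0.675: Φ(2.302 − 1.960) = 63%
- kept 0.5625: Φ(2.101 − 1.960) = 56%

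**The case against.** **The question is a strategy contrast.** The first aim compares T2T with usual practice, and two groups answer that directly. A slope per unit of T2T time answers a related but different question, and a few compliant visits need not bring proportional benefit. This stands, and it is why the two-group comparison should be kept. It does not make that comparison the most informative use of the data if benefit is roughly graded.

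**No loss figure comes from the documents.** This also stands. Each percentage needs an assumed distribution, cut and effect shape. A reader might infer that dichotomising is known to cost a fixed quarter to half of the information; the text does not support that.

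**The article does not rule out a continuous analysis.** It names no primary analysis, describes T2T effectiveness as exploratory, and does not exclude T2T time as a model term. All true. Yet the only use of T2T time that it states is to sort patients into two groups.

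**A stronger reading is tempting.** Because no cut is printed, a reader might infer that several cuts will be tried and false positives inflated. The documents do not support this. A numerical threshold is a detail that an article may leave to a fuller plan, and nothing says that the cut will be varied or chosen after outcomes are seen. One cut fixed beforehand keeps the nominal error: 5.3% in 8,000 simulated null studies of 300 patients, against 5%, which is within simulation error. A rise, for example to 8.5% when the better of cuts at 50% and 75% is taken, would require conduct that the document does not plan.

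**Conclusion.** The point holds as a matter of efficiency. Study outcomes commits to a dichotomy of an exposure that Study design scores visit by visit. With a linear effect and a uniform share of T2T time, a 50% cut loses 25% of the exposure information and a 75% cut about 33–44% (25% if only four half-year intervals are scored). The 300 patients then act like roughly 170 to 225. Under other distributions and cuts the loss runs from about 19% to 79%, and it is nil for a true step at the cut. The absence of a printed threshold is not part of the finding, and no inflation of false positives is claimed. It is a cheap improvement bearing on the first aim; it does not make the planned comparison invalid.

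**What to change.** In Study outcomes, add one sentence. The main model-based T2T analysis uses each patient's proportion of observed follow-up time that was T2T-compatible, entered as a continuous exposure in the regression and mixed models already planned. Effects are reported per 25 percentage points, with a spline to check linearity. Keep the two-group comparison with usual practice as a secondary display, using one cut fixed before outcome data are examined.

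**Cost.** No new data: the physician questionnaire after each encounter already records whether T2T was applied. An effect per 25 points (one visit interval of four, or two of eight) is less easy to read than a group difference and assumes approximate linearity.

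**What it does not cure.** Confounding remains. So does the dependence of T2T compatibility on disease control: under the stated rules a patient at target may be seen less often and needs no treatment change, so the T2T rule is easier to meet when disease is controlled. A continuous share carries that dependence into the model just as the two-group label does.

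### Classing patients as T2T or non-T2T by T2T time over the same two years as the outcomes lets disease control determine the exposure label

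*Protocol article*

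**What the plan says.** One part of the first aim is to "evaluate the impact of this therapeutic strategy in the long-term (2 year) prognosis of these patients compared to usual practice" (Protocol article, Aims of the study). Because the study is not interventional, Study outcomes builds the comparison groups from observed care: "the length of time over the two years that a patient was followed according to the T2T strategy will be used to classify patients". No cut-off is given, and no rule for patients with incomplete follow-up.

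The same section lists what is compared between the groups: "We will assess for the attainment of low disease activity and remission, as well as other treatment outcomes", the latter being quality of life, health and function indices, productivity and adverse events. Study design makes those two years the whole follow-up: "patients will be prospectively followed-up for 2 years (months 7 – 30" of the study calendar). Events are dated inside it: "all adverse events and treatment switches will be recorded at the time they occurred".

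Study design also defines when care counts as T2T. Criterion (a) is timing: "A follow-up will be considered as compatible with the T2T recommendations if: (a) the patient is re-evaluated within 3 or 6 months". Criterion (b) is that "disease activity measured using the aforementioned indices is used as a guidance for any necessary treatment modifications". Follow-up intervals and variables collected ties the timing to disease state. The maximum is 3 months at moderate or high activity, whereas "patients with low disease activity or remission may be re-evaluated every 6 months".

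Statistical analysis names multivariable regression and mixed effects models with baseline and early on-treatment predictors. It mentions no landmark, lag or time-varying T2T exposure.

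**The concern.** The exposure label is known only when follow-up ends, and it is built from the months in which the outcomes occur. This causes two separate difficulties.

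- **Reverse causation.** A patient at target meets the T2T definition by attending within 6 months, since no modification is then necessary. An off-target patient must attend within 3 months and have treatment modified. Disease control therefore adds T2T time, and disease control is then compared by T2T class.
- **Immortal time, under conditions.** If the class uses a count of T2T months, a patient whose follow-up ends early cannot accumulate many and tends to be classed non-T2T.

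At stake is the T2T-versus-usual-practice contrast. The article says that no SpA study has made this comparison beyond one year of therapy (Background) and that effectiveness in SpA is not yet proven (Anticipated results). The stated rule can give a favourable answer when T2T has no effect. Adjusting for baseline variables alone does not remove this, because the label uses information from after baseline.

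**Working it through.** The article gives no figure to reproduce here: the target of at least 300 patients carries no effect size, power or cut-off. The check asks what the stated rule yields when T2T truly does nothing.

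**1. Windows side by side.** Exposure: T2T time over the two years. Outcomes: the same two years. The overlap is complete.

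**2. How T2T time accrues.** Assumed inputs, none from the article:
- LDA prevalence 50%;
- eight quarterly periods, then an assessment at month 24 of the patient's own follow-up;
- probability of a timely visit 0.925 at target and 0.85 off target;
- probability *q* of intensification when off target, 0.3 to 0.7.

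Probability that a quarter counts as T2T:
- at target: 0.925;
- off target: 0.85 × *q* = 0.255, 0.425 and 0.595 for *q* = 0.3, 0.5 and 0.7.

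An at-target quarter is thus 0.925/0.595 = 1.6 to 0.925/0.255 = 3.6 times as likely to count.

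**3. Effect on the LDA comparison.** Activity = patient effect + visit-level noise (SD 1), with LDA when activity is below its median. T2T affects nothing. Patients are classed T2T if at least 50% or 75% of quarters count. LDA at month 24, T2T versus non-T2T:

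| Between-patient SD | *q* | Cut-off | T2T | Non-T2T | Difference (points) |
|---|---|---|---|---|---|
| 1 | 0.3 | 75% | 74.7% | 34.6% | 40.1 |
| 1 | 0.5 | 75% | 67.2% | 32.4% | 34.8 |
| 1 | 0.7 | 75% | 58.9% | 31.1% | 27.8 |
| 1.5 | 0.3 | 75% | 81.7% | 27.4% | 54.3 |
| 1.5 | 0.7 | 50% | 52.2% | 13.5% | 38.7 |
| 0 | 0.5 | 75% | 50.0% | 50.1% | −0.1 |

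Over all combinations with SD 1 or 1.5 and *q* from 0.3 to 0.7, the false difference is 27.8 to 54.3 points. In samples of 300, a two-sided 5% test then rejects in 63% to 100% of cases. With SD 0 the month-24 difference is about 0. LDA averaged over the follow-up visits still differs by about 11 to 19 points, because the same visits supply both the label and the outcome.

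**4. Immortal time.** Assumed: an exponential time to an event that ends follow-up, unrelated to T2T; T2T share of followed time ~ Beta(4.2, 1.8), mean 4.2/6 = 0.70; T2T months = share × months followed; T2T class if at least 12 months.

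| 24-month risk | T2T | Non-T2T | Risk ratio |
|---|---|---|---|
| 5% | 1.6% | 21.5% | 1.6/21.5 = 0.07 |
| 10% | 3.3% | 36.5% | 3.3/36.5 = 0.09 |
| 20% | 6.8% | 56.8% | 6.8/56.8 = 0.12 |

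The true ratio is 1. Classing the same patients by *share* of followed time gives about 1.0. So does an event that does not end follow-up.

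**5. Does a landmark repair step 3?** Same model, T2T share in months 0–12 against LDA at month 24: the false difference is still about 23 to 48 points. Stratifying also on LDA status at the visits in that window brings it to within about 1 point of 0.

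**The case against.** The strongest reply concerns immortal time. The article never says that patients who leave early become non-T2T. It gives neither a cut-off nor a rule for incomplete follow-up, and a condensed article may leave both to a fuller document. A share-based class is as open as a count of months, and it removes the artefact. The listed outcomes are mostly scores at repeated visits, and neither death nor dropout is among them. Recording adverse events and switches as they occur suggests that follow-up usually continues through them. All of this stands. A reader might infer that the risk ratios of 0.07 to 0.12 measure the bias to expect; they describe one reading of the rule and one kind of event.

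A reader might also infer that T2T must look protective whatever the truth. The document does not support that either: without persistence in disease activity, LDA at month 24 is unaffected.

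Finally, the design is openly non-interventional, no primary outcome is named, and the comparison is one part of the first aim, beside the extent of implementation and the reasons for non-implementation. That limits the reach of the point but does not answer it. The overlap of windows, and the easier accrual of T2T time at target, follow from rules that the article itself fixes. An analysis plan with a lagged or time-varying exposure would replace the stated rule, not fill it in.

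**Conclusion.** The concern holds, with reverse causation as the main mechanism. Applied as written, the classification biases the comparison in favour of T2T whenever disease activity persists within patients. Under the assumed inputs the false difference in LDA at month 24 is about 28 to 54 points; with no persistence it is about 0. The size depends on LDA prevalence, persistence, the intensification probability and the cut-off, none of which the article states. The direction was the same wherever the bias appeared.

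Immortal time is secondary. It needs both absolute T2T months and an event that ends or shortens follow-up. For scores measured at month 24 the issue is reverse causation and time-varying confounding by disease activity.

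The rule should be changed before analysis, because the favourable result it can produce is the one the study sets out to test.

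**What to change.** Replace the end-of-study classification in Study outcomes, and carry the change into Statistical analysis.

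- **Preferred.** Record T2T status at each visit. Relate status up to visit *k* only to outcomes after visit *k*, adjusting for disease activity (ASDAS, DAPSA or LDA status) and treatment up to visit *k*. A marginal structural model or a sequence of emulated trials would do this.
- **If one label per patient is wanted.** Use a landmark: T2T share of followed time in an early window, for example months 0–12, entered as a continuous variable. Relate it to later outcomes in patients still followed, adjusting for disease activity at the visits in that window. A landmark without this adjustment is not enough.
- **Adverse events.** Report rates per person-time by current T2T status.

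The cost is more analysis work and no new data, since disease indices are collected at each visit and treatment switches and adverse events are recorded as they occur. The landmark version drops early-window outcomes from the comparison and applies only to patients still followed at the landmark.
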